### Stage 3: model evaluation, longitudinal risk prediction using NHS England (aka digital) data

In the final stage, the local Hospital dataset was linked with NHS England longitudinal records, which include confirmed cardiovascular events. The performance of ML score to predict clinical events will be evaluated against base models of QRISK3, and SE ischaemia positivity. The forecasting power of future cardiovascular events over 5-year and 10-year will be assessed.

This longitudinal modelling framework enables dynamic risk prediction and supports early identification of individuals at elevated risk of adverse cardiovascular outcomes. We will be inviting external sites for validation and testing the robustness and scalability of the developed predictive algorithm in all spectra of SE modalities.

Internal validation once completed external validation is performed using independent multicentre cohorts, including EVAREST and Stress Echo 2030 to assess generalisability of the model. Model discrimination will be assessed using the area under the receiver operating characteristic curve (AUC) with 95% confidence intervals (CIs). Calibration will be evaluated using calibration-in-the-large, calibration slope, observed-to-expected event ratios, calibration plots, and the Brier score. Where systematic miscalibration is identified, model recalibration using intercept and slope adjustment will be undertaken prior to assessing clinical utility by. using risk reclassification analyses, including the net reclassification improvement (NRI).

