### Outcomes

All-cause death, hard endpoints: cardiovascular death, non-fatal myocardial infarction (MI) and composite outcomes will provide with different major cardiovascular events (MACEs), including stroke and unplanned revascularization, and hospital admission with progressive angina (MACE, 3-4-5) across four time periods: 1–3 years, 3–5 years, 5–10 years, and 10–20 years. The outcome data will be derived from NHS -England database with linking patients’ data such as NHS number and DOB and date of SE over 17 years after the indexed SE. (DARS-NIC-662451-S5L8J-v0.16).

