### Stage 1: clinical risk modelling and baseline assessment

#### QRISK3 risk estimation

QRISK3 is a validated clinical risk prediction model designed to estimate the 10-year risk of cardiovascular disease (CVD) using demographic and clinical variables.^11^ In this study, QRISK3 is used as a benchmark model against which ML-based approaches are evaluated.

Relevant patient characteristics and CAD risk factors were extracted from the local Hospital dataset and processed using the QRISK3 framework. The resulting risk estimates provide a clinically interpretable baseline for comparison with ML predictions (details of data extraction is provided in the Supplement).

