**Figure 2 qyag143-F2:**
[figure not shown]
FINESSE—machine learning model development workflow.

Baseline risk for each patient will be defined using conventional clinical assessment and QRISK3 derived estimates, as previously described. FINESSE AI will then generate an updated, individualized probability of the outcome of interest at a specified time horizon by integrating echocardiographic parameters, haemodynamic response variables, clinical characteristics, and longitudinal data. The integrated risk estimate will be defined as:

$$R_{F}(i,t)=f(R_{0}(i,t),X_{e}(i),X_{h}(i),X_{c}(i),X_{l}(i))$$

where $R_{0}(i,t)$ represents the baseline risk estimate and the additional inputs correspond to echocardiographic, haemodynamic, clinical, and longitudinal variables, respectively.

To facilitate clinical interpretation, continuous risk estimates will be mapped to predefined categories using a threshold-based classification function. These thresholds will be prespecified and subsequently evaluated against observed event rates within the study cohort to ensure appropriate calibration defined as low risk–intermediate risk–high risk.

Risk reclassification will be defined as a change in category between baseline and FINESSE-derived estimates, expressed as the difference between the categorical assignments derived from $R_{F}(i,\;t)$ and $R_{0}(i,\;t)$. Reclassification will therefore reflect either upward or downward movement across predefined risk strata. To minimize clinically insignificant shifts, reclassification will only be considered when the absolute change in predicted risk exceeds a predefined threshold, anticipated to be in the range of 3–5 percentage points. The predefined 3–5% risk reclassification threshold was selected because it represents the range within which relatively small improvements in estimated cardiovascular risk may influence guideline-directed management decisions, including initiation or intensification of lipid-lowering therapy, additional diagnostic testing, or referral for invasive coronary angiography. Similar thresholds have been adopted in previous cardiovascular risk prediction studies evaluating improvements in discrimination and clinical utility through net reclassification analyses. The threshold was therefore chosen to maximize clinical relevance rather than statistical optimization alone.

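### Reclassification against QRISK3 has no defined baseline risk at 5 years or on the study endpoints, and recalibration before NRI is stated for the model with no matching step for QRISK3

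*Protocol article*

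**What the plan says.** The section on QRISK3 risk estimation gives the benchmark one horizon: "QRISK3 is a validated clinical risk prediction model designed to estimate the 10-year risk of cardiovascular disease (CVD". The Outcomes section lists different endpoints: all-cause death, cardiovascular death, non-fatal MI, and MACE composites that can include stroke, unplanned revascularization and admission for progressive angina, "across four time periods: 1–3 years, 3–5 years, 5–10 years, and 10–20 years". Stage 3 adds: "The forecasting power of future cardiovascular events over 5-year and 10-year will be assessed".

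The section on the FINESSE AI risk reclassification framework sets the baseline: "Baseline risk for each patient will be defined using conventional clinical assessment and QRISK3 derived estimates, as previously described". The FINESSE estimate is an "individualized probability of the outcome of interest at a specified time horizon". Both are written with the same index, as R0(i,t) and RF(i,t), and reclassification is "expressed as the difference between the categorical assignments derived from" the two. A movement counts only if the predicted risk changes by more than a minimum amount, "anticipated to be in the range of 3–5 percentage points". The end of that section names AUC, calibration plots, Brier scores, NRI and IDI as the measures of incremental value.

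The external-validation paragraph of Stage 3 lists AUC and calibration measures, including the Brier score, and continues: "Where systematic miscalibration is identified, model recalibration using intercept and slope adjustment will be undertaken prior to assessing clinical utility". NRI comes after that step. For QRISK3, the section on baseline performance evaluation plans a calibration analysis but states no recalibration.

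**The concern.** NRI, IDI and Brier respond to the level of predicted risk as well as to the ranking of patients. If two scores rank patients identically but one is on the wrong horizon, on another endpoint, or uncorrected for the local event rate, all three can differ although neither score carries more information.

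The article leaves that open in two places. First, R0(i,t) is needed at each horizon t, but the only source named for a numerical baseline risk is a 10-year one, and its endpoint is not the study's. At 5 years there is no stated R0. At 10 years the horizon matches but the endpoint does not. Second, the model under validation may be updated on the external data before NRI is calculated, with nothing equivalent stated for the comparator. The resulting NRI would describe a locally updated model, whereas the stated aim of external validation is generalisability.

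At stake is whether a reported reclassification gain, or loss, against QRISK3 can be read as a difference in predictive content.

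**Working it through.** The article gives no NRI, IDI, Brier or event-rate figure on this point, so there is nothing to reproduce. The check asks what the metrics show when the new score has exactly the same ranking as QRISK3, so that the AUC difference is zero by construction.

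**Inputs from the article.** QRISK3 median 8.4, quartiles 3.4 and 15.2 (Table 1); QRISK3 horizon 10 years; assessment at 5 and 10 years; minimum change 3 to 5 points.

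**Assumptions.** Category cut-offs of 5%/10% or 10%/20%; constant hazard; true hazard equal to m times the QRISK3 hazard, with m = 1, 1.5 or 2.

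**Formulas.**
- QRISK3 risk q: log-normal, median 0.084, SD of log risk = ln(15.2/3.4)/1.349 = 1.11, capped at 0.80; 2,000,000 draws.
- Hazard h = -ln(1-q)/10; true risk at t: p = 1 - exp(-m·h·t).
- Baseline score = q; new score = p, the same ranking put on the correct level.
- NRI = [P(up|event) - P(down|event)] + [P(down|non-event) - P(up|non-event)].
- Brier = mean of p(1-r)² + (1-p)r² for score r; IDI = new minus baseline difference in mean risk between events and non-events.

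**One patient.** With q = 8.4% and m = 1, the 5-year risk is 1 - (1-0.084)^0.5 = 4.3%. The change is 8.4 - 4.3 = 4.1 points and crosses a 5% cut-off. It counts under a 3-point rule and not under a 5-point rule, although nothing about the patient is better known.

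**Results.**

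| Scenario (identical ranking) | Brier, baseline to new | NRI, cut-offs 5/10% | NRI, cut-offs 10/20% |
|---|---|---|---|
| 5 years, m = 1 | 0.0710 to 0.0632 | +0.17 (events -0.29, non-events +0.45) | -0.07 |
| 5 years, m = 1.5 | 0.083 to 0.081 | +0.09 | -0.01 |
| 5 years, m = 2 | no difference | 0 | 0 |
| 10 years, m = 2, only the new score recalibrated | 0.145 to 0.131 | -0.29 | about -0.1 |

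The NRIs in the table are without the minimum-change rule. In the first row the observed/expected ratio of the baseline is 0.56, IDI is -0.08, and Brier falls by (0.0710 - 0.0632)/0.0710 = 11%. With cut-offs 5/10% the NRI there becomes +0.12 under a 3-point rule and +0.02 under a 5-point rule. In the third row the effects cancel: doubled hazard over 5 years equals the QRISK3 hazard over 10. In the last row IDI is +0.08 while NRI is negative.

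**Second calculation.** A logit-normal draw was used, with true odds k times the QRISK3 odds.
- At 5 years with only the horizon mismatched, and the 3 to 5 point rule applied, total NRI ran from -0.17 to +0.07 depending on cut-offs (5/10%, 10/20% and 5/20%). IDI was -0.061 and Brier went from 0.0650 to 0.0587.
- At 10 years with one side recalibrated and k from 0.5 to 3, IDI ran from -0.051 to +0.073 and total NRI from -0.31 to +0.08. Brier fell by 0.0007 to 0.025.
- With both scores on the same horizon and both recalibrated, NRI, IDI and the Brier difference were all 0 (Brier 0.0587 for each at 5 years).

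**Limit of the match to Table 1.** The simulated quartiles are 4.0 and 17.7 (log-normal) and 3.9 and 17.1 (logit-normal), somewhat wider than 3.4 and 15.2.

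**The case against.** A reader might infer that the article sets a 10-year QRISK3 risk against a 5-year machine-learning risk. It does not say so. R0 and RF share the index t, so a common horizon is intended, and the 10-year comparison has one. R0 also draws on conventional clinical assessment, so it need not be the raw score. What stands is narrower: the article names no method for obtaining R0 at 5 years or on the study endpoint. Nor does it link the four outcome periods to the reclassification step.

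A reader might also infer that only the machine-learning model is recalibrated. That is the natural reading of a paragraph about the generalisability of the developed model, but it is not stated. The step is conditional on miscalibration being found. AUC and calibration of the untouched model, including its Brier score, are already planned before it, so the objection to updating on external data applies to the NRI step.

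A third tempting reading is that the arrangement favours machine learning. The figures do not support this. Brier favoured the correctly scaled score wherever the two differed, but NRI and IDI went either way, and one-sided recalibration at 10 years with doubled hazards gave an NRI against the recalibrated model. At 5 years with doubled hazards there was no effect at all.

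Finally, this is a condensed article, and a full analysis plan may settle horizon conversion and recalibration. The exact minimum-change value is largely a detail for that plan: the range is labelled as anticipated and is not pressed here. The comparator, the horizons and the placing of recalibration before NRI are fixed in the article itself, and as written they do not fit together.

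**Conclusion.** The point holds as a gap in how the comparison with QRISK3 is specified. As written, NRI, IDI and Brier differences can arise from horizon, endpoint or calibration mismatch with no gain in prediction. In the simulations with identical ranking, the 5-year NRI ranged from +0.17 to -0.07 with the choice of cut-offs when QRISK3 was taken as correct at 10 years, and was zero when true hazards were twice as high. Size and direction rest on assumed cut-offs, constant hazard and an approximate match to Table 1; the article gives neither event rates nor cut-off values. The endpoint mismatch was not simulated separately.

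It would go too far to call the evaluation uninterpretable. AUC is unaffected, the 10-year horizons match, untouched external AUC and calibration are planned, and no metric is named as the main one.

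**What to change.** 1. **Baseline.** Enter the transformed QRISK3 risk as the single covariate of a Cox model for the study endpoint in the development data. Use that model's 5- and 10-year predictions as R0(i,t), so that R0 and RF share endpoint and horizon.
2. **External cohorts.** Report NRI, IDI and Brier first for both models untouched, beside the AUC and calibration measures already planned. If recalibration is added, apply the same intercept and slope update to QRISK3 and the machine-learning model, and label those results as describing locally updated models.

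The cost is revised wording and a few extra model fits. The reported difference from QRISK3 may change in either direction. The change should be made before outcomes are analysed.

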### Statistical methods

Participant demographics and characteristics are summarized with descriptive statistics. Categorical variables are expressed as median (interquartile range), and continuous variables are expressed as mean (standard deviation). Internal model validation will be performed with 5-fold cross-validation. Cox-regression model was fitted to estimate the hazard rates, hazard ratios (HR) and the 95% CIs. Survival probabilities from any event for the first time since SE will be evaluated using Kaplan–Meier curves. Performance evaluation for the model will include measurements of Accuracy alongside Sensitivity and Specificity, using receiver Operating Characteristic (ROC) analysis with c-statistics, together with calibration plots and risk reclassification. The study will perform comparative assessments between ML models and the QRISK3 calculator to evaluate their incremental predictive value. Statistical analyses will be performed using Stata 18.0 (StataCorp LP, College Station, TX) and the R environment (R 4.5.1, The R Foundation for Statistical Computing, http://www.R-project.org) using R studio (version 2024.12.1). All tests were two-sided and α was set at 0.05, unless specified otherwise.

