In instances where FINESSE-derived risk estimates are discordant with conventional diagnostic findings, such as a low-risk SE profile in the presence of an elevated predicted risk, cases will be flagged for clinical review rather than automatically reassigned. This approach is intended to preserve alignment with established diagnostic pathways and ensure that model outputs are interpreted within the broader clinical context.

Rather than replacing current clinical assessment, the FINESSE framework is intended to function as a decision-support system embedded within routine SE reporting. Following completion of image interpretation, the algorithm automatically integrates demographic, clinical, laboratory, ECG and echocardiographic parameters to generate an individualized risk estimate. This risk estimate may assist clinicians in identifying patients who would benefit from intensified preventive therapy, further anatomical imaging, closer surveillance, or expedited invasive investigation while preserving final clinical judgement.

The incremental value of the FINESSE AI reclassification framework will be evaluated by comparing baseline and model-derived predictions using discrimination metrics, including the AUC, alongside calibration assessment using calibration plots and Brier scores. In addition, reclassification-specific metrics, including NRI and integrated discrimination improvement, will be used to quantify the extent to which FINESSE AI enhances patient stratification beyond conventional approaches.

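### Clinical utility is to be judged by reclassification (NRI), which weights false positives by the event rate and not by the decision threshold; net benefit should be the utility measure

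*Protocol article*

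**What the plan says.** In the Stage 3 section, if systematic miscalibration is found, "model recalibration using intercept and slope adjustment will be undertaken prior to assessing clinical utility". The same sentence then names the method: "assessing clinical utility by. using risk reclassification analyses, including the net reclassification improvement (NRI".

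The section on the FINESSE AI–based risk reclassification framework makes the link again. It supports its minimum-change rule by citing earlier studies "evaluating improvements in discrimination and clinical utility through net reclassification analyses". The rule itself is "anticipated to be in the range of 3–5 percentage points". Of the low, intermediate and high category cut-offs it says: "These thresholds will be prespecified and subsequently evaluated against observed event rates within the study cohort". No numerical values are given. The decisions that a change in estimated risk might alter are "initiation or intensification of lipid-lowering therapy, additional diagnostic testing, or referral for invasive coronary angiography".

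The same section ends by saying that "reclassification-specific metrics, including NRI and integrated discrimination improvement, will be used to quantify the extent to which FINESSE AI enhances patient stratification", alongside AUC, calibration plots and Brier scores. Statistical methods lists accuracy, sensitivity, specificity and c-statistics, "together with calibration plots and risk reclassification". Net benefit, a decision curve, a weighted NRI or a relative cost of a false positive appears nowhere.

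**The concern.** A claim of clinical utility is a claim that acting on the new risk estimate at a given cut-off leaves patients better off than acting on the old one. It needs an exchange rate between an event caught and a false alarm raised, and the cut-off supplies one: acting at risk t means accepting (1-t)/t false positives for each true positive. NRI takes its exchange rate from how common the event is, whatever the cut-off. It is a summary of movement between categories and not a measure of utility.

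This matters here because the listed decisions run from lipid-lowering therapy to referral for invasive angiography, where a false positive has very different consequences. A single NRI weights them all alike. The framework is presented as decision support within routine SE reporting, so a reported gain in utility with the wrong sign at a cut-off in use would be a substantive error.

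**Working it through.** **Inputs.** The article gives no event rate (Sample size calculation says only that events should be frequent enough) and no category cut-offs. There is no figure of the plan's to reproduce. Event rates and cut-offs below are assumptions.

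**Formulas, one cut-off.** Let p be the event rate, t the cut-off, dS the change in sensitivity (net share of events moved up) and dF the change in false-positive rate (net share of non-events moved up).

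- NRI = dS - dF
- Change in net benefit = p·dS - [t/(1-t)]·(1-p)·dF

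Multiplying NRI by p gives p·dS - [p/(1-p)]·(1-p)·dF. This is the net-benefit formula with the odds of the event rate in place of the odds of the cut-off. The signs must therefore agree when t = p and need not agree otherwise.

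**Worked case.** p = 0.10, dS = 0.15, dF = 0.10, so NRI = 0.15 - 0.10 = +0.05. Per 1000 patients there are 1000 × 0.10 × 0.15 = 15 more true positives and 1000 × 0.90 × 0.10 = 90 more false positives. Change in net benefit per 1000 = 15 - 90·t/(1-t):

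| Cut-off t | t/(1-t) | False-positive cost | Change in net benefit per 1000 |
|---|---|---|---|
| 5% | 0.0526 | 4.7 | +10.3 |
| 10% | 0.1111 | 10.0 | +5.0 |
| 15% | 0.1765 | 15.9 | -0.9 |
| 20% | 0.2500 | 22.5 | -7.5 |

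Break-even is where t/(1-t) = 15/90, that is t = 1/7, or about 14.3%. NRI is +0.05 in every row.

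**Cut-off below the event rate.** p = 0.30, t = 0.10, dS = -0.06, dF = -0.10. NRI = -0.06 + 0.10 = +0.04. Per 1000 there are 18 fewer true positives and 70 fewer false positives, so the change is -18 + 70/9 = -10.2. The disagreement is not confined to high cut-offs.

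**Break-even ratios.** NRI breaks even at dF/dS = 1. Net benefit breaks even at p(1-t)/[t(1-p)]: 0.44 for p = 10%, t = 20%; 0.26 for p = 10%, t = 30%; 0.47 for p = 5%, t = 10%.

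**Do the plan's safeguards remove it?** This was checked by simulating 1,000,000 patients, with a model that contains the baseline predictor, recalibration by intercept and slope, and assumed cut-offs of 10% and 20%. In one setting with 10% events and a true risk curved in the predictor:

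| Minimum change | Three-category NRI | Net benefit per 1000 at 10% | at 20% |
|---|---|---|---|
| none | +0.021 | +3.8 | -2.7 |
| 3 points | +0.017 | +2.8 | -2.2 |
| 5 points | +0.005 | +1.1 | -1.6 |

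So recalibration and the minimum-change rule can leave a positive NRI beside a loss at one cut-off and a gain at the other. In another curved setting with 20% events and no minimum change, NRI was -0.017 while net benefit rose at both cut-offs (+0.5 and +2.0), so NRI can also hide a gain. Where the model was correctly specified, NRI and net benefit were both positive.

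**The case against.** The strongest reply is that the article is a condensed account. It says reclassification analyses including NRI, which leaves the list open, and a decision curve could sit in an analysis plan that is not shown. AUC, calibration and Brier score stand beside NRI, so no conclusion hangs on NRI alone. The worked shifts, event rate and cut-offs are hypothetical, and net benefit is positive at two of the four cut-offs tabulated.

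Much of this stands and limits the point. It does not remove it: the article itself chooses the measure that carries the label of clinical utility, and none of the measures named beside it weights errors at a threshold. Sensitivity and specificity would allow net benefit to be derived, but that is not planned.

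Four stronger readings are tempting and are not supported.

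- A reader might infer that NRI ignores false positives. It counts them, through non-events moved up; only the weight is wrong for this purpose.
- A reader might infer that IDI is also offered as a utility measure. The article presents it as a measure of stratification.
- A reader might infer that the whole case for FINESSE rests on NRI and IDI. The measures listed above contradict that.
- A reader might infer that NRI would reward useless predictors under this plan. In a simulation with 30 pure-noise predictors, 1810 development patients (80% of 2263), 20% events and cut-offs of 5% and 10%, mean NRI was +0.026 without recalibration. After intercept-and-slope recalibration it was -0.048, positive in 4% of runs. The plan recalibrates where systematic miscalibration is identified, so this argument should not be used.

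**Conclusion.** The point holds in this form: the article names reclassification, including NRI, as its assessment of clinical utility, and NRI does not measure that. Its sign is guaranteed to match net benefit only when the cut-off equals the event rate. In the illustration the same NRI of +0.05 goes with anything from +10.3 to -7.5 per 1000 over cut-offs of 5% to 20%.

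The size rests on an assumed 10% event rate and assumed shifts; the algebra rests on neither. Net harm is possible, not certain. A model that contains the baseline risk and is calibrated at every risk level would not lose net benefit, but intercept-and-slope adjustment does not guarantee calibration at each cut-off. The plan should be changed on this point, and can be: the article defers the quantitative performance results to a later manuscript.

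**What to change.** In the Stage 3 section and at the end of the reclassification framework section:

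- Name net benefit (decision-curve analysis) as the measure of clinical utility, evaluated at the prespecified category cut-offs. The investigators need to state those cut-offs; none is proposed here.
- Compute it out of sample, in the same patients, for FINESSE, QRISK3, SE positivity, treat-all and treat-none, with bootstrap 95% confidence intervals.
- Report NRI as separate event and non-event components. Describe NRI and IDI as measures of stratification, not as evidence of clinical utility.

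The cost is a little more analysis code and revised wording, with no new data. The downside for the investigators is that the reported gain may be smaller than the NRI suggests.
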